### General procedures and monitoring

#### Data collection and management

Treatment-related data are collected at V1 (before intervention) and at V2 (the start of the intervention or the baseline). According to the study protocol, follow-up data will be collected from V1 to months 6 (V3) and 12 (V4). Data collection begins on the day a participant signs the informed consent and continues until the termination of the trial or until the participant withdraws from the trial for any reason. If participants discontinue or deviate from the study protocols, the investigators will attempt to minimize the missing data. All original data are kept in chronological order for verification. Original data are transferred in a timely manner to a paper-based case report form (CRF) and an electronic database system located in a guarded facility at the trial site. Access to the study data is restricted. The PI will have access to the final dataset. An independent steering committee will monitor and examine adherence to the study protocol (Figs. 1 and 2).

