### Withdrawal criteria

If adverse events, especially severe adverse events, occur, researchers may consider withdrawal of patient(s) based on ethical and safety concerns.Patients drop out of the study.Patients voluntarily withdraw their informed consent.Serious violation of the study protocol by the subjects or investigators.Other reasons that the researchers believe are acceptable reasons for quitting the study.

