### Data analysis

Normally distributed variables will be expressed as the mean and standard deviation (SD), and non-normally distributed variables will be expressed as the median and interquartile range; categorical variables will be expressed as the number and percentage (*n*, %). In test groups with continuous normally distributed variables, Student’s *t*-test will be used; the Mann–Whitney U test will be used for continuous non-normally distributed data. Categorical variables will be compared with the χ2 test or Fisher’s exact test; when appropriate, categorical variables will be reported as the relative risk. The statistical analyses will be conducted on an intention-to-treat basis. Multivariable analysis will be conducted by logistic regression and generalized mixed linear regression models with adjustment for any possible confounding covariates and with consideration of within-center variability. A *p* value of < 0.05 will be considered statistically significant.

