### Populations for evaluation and missing data management

All evaluations, in particular the evaluation of the primary outcome measure, will be made with data from all randomized patients, regardless of whether they adhered to the treatment protocol or provided complete data sets. In particular, the following patients may be missing data:Those who discontinued the clinical trial will be evaluated as if they had completed the trial.Those whose planned examinations were not performed within the planned time frame will still be taken into consideration in the analysis.Patients who withdraw their consent to use their personal data for statistical analyses will be excluded from the analysis.Missing individual responses on the Quality of Life Questionnaire II will be replaced by simple imputation according to the recommendations in the test manual.

The reasons for any missing data will be analyzed, and any random missing data will be handled by the application of multiple imputation and model-based approaches, such as mixed models or weighted generalized estimating equations for repeatedly measured outcomes. Sensitivity analyses will be performed to examine the robustness of the results with reference to the assumptions made in the complete case analysis.

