### Adverse events

An adverse event (AE) refers to any untoward event that occurs during the clinical study but that does not necessarily have a causal relationship with the surgical treatment. Safety evaluations are performed from the point at which the signature on the informed consent form is obtained until the end of the study or until the patient withdrawal from the trial, according to the management requirements. AEs and serious adverse events (SAEs) will be reported.

An SAE is an event that causes hospitalization, prolonged hospitalization, disability, incapacity, life-threatening illness or death, or congenital malformation during the clinical trial.

During the study, all AEs will be recorded. These records include the type of AE (using standard medical terminology), the date of the occurrence of the AE, the date of the disappearance/stabilization of the AE, the severity of the AE, the impact of the AE on the surgery, the relationship of the AE with the surgery, the treatment measures, and the outcomes. If an SAE occurs, researchers fill in an SAE report form. The report is signed and dated and reported to the ethics committee of the Corporate Fund University Medical Centre (UMC) and the clinical research centre of the National Scientific Centre for Oncology and Transplantation (Astana, Kazakhstan) within 24 h.

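### Data and safety collection end at any withdrawal, including one imposed by investigators, which conflicts with the promised intention-to-treat analysis of all randomized patients

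*Protocol article*

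**What the plan says.** All references are to the Protocol article.

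- **Withdrawal criteria** lists five grounds. Two are the patient's own act: dropping out and withdrawing consent. The other three can be imposed: "If adverse events, especially severe adverse events, occur, researchers may consider withdrawal of patient(s) based on ethical and safety concerns"; "Serious violation of the study protocol by the subjects or investigators"; and "Other reasons that the researchers believe are acceptable reasons for quitting the study".
- **Data collection and management** says that collection starts at consent and "continues until the termination of the trial or until the participant withdraws from the trial for any reason". The next sentence says that investigators will try to limit missing data when participants discontinue or deviate. It names no procedure.
- **Adverse events** runs safety evaluation from consent "until the end of the study or until the patient withdrawal from the trial, according to the management requirements".
- **Data analysis** states: "The statistical analyses will be conducted on an intention-to-treat basis".
- **Populations for evaluation and missing data management** includes every randomized patient "regardless of whether they adhered to the treatment protocol or provided complete data sets". Patients who discontinued are to be evaluated like completers, and only those who withdraw consent to use of their data are excluded. Missing data that are random are to be handled by multiple imputation and model-based methods. Sensitivity analyses are planned, with reference to complete-case assumptions.

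**The concern.** An intention-to-treat analysis needs outcomes from patients who did not follow the plan, because they are part of the randomized comparison. Here the analysis sections keep such patients in, while the conduct sections allow collection of their outcomes to stop.

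The permitted reasons for stopping (harm, serious violation, investigator judgement) are plausibly related to the treatment received and to the outcome. They may also arise differently under two operations and a diet, so losses need not balance across arms.

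Two things are at stake: telomere length and the secondary outcomes at months 6 and 12, and adverse events that first appear after withdrawal. An analysis plan written later cannot recover blood samples that were never drawn or events that were never recorded.

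**Working it through.** The point is a conflict between stated rules, so the main check is to trace one patient through them.

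1. A patient is randomized and, before month 6, is withdrawn by the investigators for a serious violation. The Withdrawal criteria permit this even if the violation was an investigator's.
2. Under Data collection and management, withdrawal for any reason ends collection. The month 6 (V3) and month 12 (V4) assessments are not required. The patient has baseline data and no later telomere measurement. If withdrawal falls after month 6, V3 is kept and V4 is lost.
3. Under Populations for evaluation, the same patient must be analysed like a completer, because consent to data use still stands.
4. Steps 2 and 3 meet only if the missing outcome is imputed or modelled. The methods named are for random missing data, and the reason in step 1 is plausibly not random with respect to outcome. The sensitivity analyses refer to complete-case assumptions and do not name outcome-related withdrawal.
5. Under Adverse events, safety evaluation also stops at withdrawal, so a new event afterwards is not recorded. The same section asks for the resolution or stabilization date and the outcome of every event. For an event still open at withdrawal, those two requirements pull apart.

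**Size.** The plan's figure is 60 patients, 3 × 20. Nothing beyond that sum can be reproduced, because the article gives no effect size, SD, power or dropout rate. With 20 per arm, one lost patient is 1/20 = 5% of the arm.

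The rest is illustration. Inputs: n = 20 per arm (Randomization) and alpha 0.05 (Data analysis). Assumptions: two-sided test, 80% power, loss of 0 to 30% per arm, and withdrawn patients differing from completers by s = 0.5 SD.

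- Detectable pairwise difference, normal approximation: (1.960 + 0.842) × √(2/n) SD. At n = 20 this is 2.802 × 0.3162 = 0.886.
- Complete-case bias in an arm mean: the full mean is (1 − w) × completer mean + w × withdrawn mean, so using completers alone is off by w × s, with w the fraction lost.

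| Lost per arm | n observed | Detectable difference (SD) | Power for 0.886 SD | Bias w × 0.5 (SD) |
|---|---|---|---|---|
| 0% | 20 | 0.886 | 80% | 0 |
| 10% | 18 | 0.934 | 76% | 0.05 |
| 20% | 16 | 0.991 | 71% | 0.10 |
| 30% | 14 | 1.059 | 65% | 0.15 |

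The exact t-test gives slightly larger detectable differences: 0.909 SD at 20 per arm and 1.024 SD at 16. The precision columns would look the same for any cause of loss, so they do not isolate investigator-imposed withdrawal. The finding does not depend on them.

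**The case against.** The strongest defence has five parts.

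- **The article already distinguishes deviating from withdrawing.** The sentence on limiting missing data concerns participants who discontinue or deviate, and it shows intent. But it does not say that visits continue after withdrawal, and it directly follows a stopping rule that covers any reason.
- **Withdrawing might mean only the patient's own choice.** The Withdrawal criteria make voluntary withdrawal of consent one of five grounds. At best the wording is ambiguous, and the ambiguity needs resolving.
- **Withdrawal is not automatic.** This stands. Adverse events only allow investigators to consider withdrawal, and only serious violations are listed. A reader might infer that a patient who abandons the diet, or has a surgical complication, leaves the dataset by rule. The article does not say so. It expects non-adherent patients to be analysed, and data collected before withdrawal are kept.
- **Intention-to-treat can still be done.** This also stands. A reader might infer that the promised analysis cannot be delivered, or shrinks to a per-protocol comparison. Neither follows: every randomized patient whose data may be used can be analysed in the allocated arm by multiple imputation, mixed models or weighted estimating equations. What is lost is observed outcomes after withdrawal.
- **Safety capture is largely intact.** All adverse events are to be recorded and serious ones reported within 24 hours, so the event that prompts a withdrawal should be captured. The gap concerns later, new events and follow-up of events still open.

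The condensed article format excuses missing retention procedures. It does not excuse rules that are stated and conflict.

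**Conclusion.** The conflict is real and lies in the stated text. The Withdrawal criteria, Data collection and management, and Adverse events together permit outcome and safety collection to end for reasons linked to treatment, while the analysis sections promise a comparison of everyone randomized. For patients withdrawn in this way, intention-to-treat would rest on a missing-at-random assumption that their reasons for withdrawal make doubtful.

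The extent cannot be stated, because the article gives no withdrawal rate and investigator-imposed withdrawal for adverse events is discretionary. What is firm is that each lost patient is 5% of a 20-patient arm. The bias of 0.05 to 0.15 SD holds only under the assumed 10 to 30% loss, the assumed 0.5 SD gap and a complete-case analysis. The planned models may reduce it. The correction is worth making because it is cheap and the data cannot be recovered afterwards.

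**What to change.** Reconcile Withdrawal criteria, Data collection and management, Populations for evaluation, and Adverse events:

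- Define discontinuation of the allocated treatment and withdrawal of consent to follow-up as two separate events.
- State that protocol violation, adverse events and other investigator reasons do not end data collection.
- Continue the scheduled V3 and V4 assessments and adverse-event recording for every randomized patient who has not withdrawn consent to follow-up.
- Record treatment discontinuation and any cross-over, with date and reason, as data.

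This concerns data collection only; it changes no treatment decision. The cost is an amendment through the ethics committee and modest effort to bring non-adherent patients back. The visits are already scheduled, and no new patients or endpoints are needed. Some outcomes will still be missing where consent is withdrawn or patients are lost, so the planned missing-data methods remain necessary.

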**Fig. 1 Fig1:**
[figure not shown]
Study design (LIFEXPE-RT). *%EWL* percentage of excess weight loss

**Fig. 2 Fig2:**
[figure not shown]
General procedure and monitoring process (flow diagram of the study design for the study entitled “A study of the life expectancy of patients with metabolic syndrome after weight loss: a comparative randomized controlled clinical trial”)

### Outcome measures

#### Primary outcome measurement

Changes in the length of leukocyte telomeres

Changes in leukocyte TL will be determined in the patients in the three groups 6 and 12 months after surgery.

#### Secondary outcome measurements

2.Change in body mass index (**Δ** BMI)

This measurement assesses the change in BMI after the intervention. Weight (kg) and height (cm) will be combined in the BMI (kg/m^2^). The time frame is baseline, 6 months, and 12 months after surgery.3.Changes in comorbidities

Changes in comorbidities will be assessed according to evaluation of the relevant symptoms and reported as the percentage of patients in whom there is an improvement in or resolution of diabetes, hyperlipidemia, hypertension, and obstructive sleep apnoea 6 and 12 months after surgery.4.Changes in quality of life

Quality of life measured by the Moorehead-Ardelt questionnaire (Quality of Life Questionnaire II) 6 and 12 months after surgery.

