### Eligibility criteria

The inclusion criteria are as follows:Aged from 18 to 55 years.BMI from 30 to 50 kg/m^2^.Metabolic syndrome (MetS) with abdominal adiposity according to the presence of at least two of the following components of MetS: increased fasting plasma glucose levels detected before diabetes to pre-diabetes (HbA1 = 5.7–6.4 or a threefold increase in fasting plasma glucose > 5.6 mmol/l); previously diagnosed type 2 diabetes (HbA1 > 6.5 or glucose > 6.1); arterial hypertension (AD 130/85 mmHg or receiving antihypertensive therapy); increased triglyceride levels (> 1.7 mmol/L or receiving specific treatment for this disorder); decreased levels of high-density lipoprotein cholesterol (HDL-C < 1.03 mmol/L in men and < 1.29 mmol/L in women or receiving treatment for this disorder). The patient population will be included in the study if inadequately controlled despite optimal treatment for their diabetes, hypertension, and lipid disorders.Available to receive treatment for 6 months, with the possibility of follow-up.Provided written informed consent for randomization and treatment.

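### Comorbidity change is judged by symptoms although entry defines three of the four conditions by measurement or treatment, and the percentages are not limited to patients who have the condition

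*Protocol article*

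**What the plan says.** In the protocol article, the section on secondary outcome measurements gives both the basis for judging change and the measure reported. Change is "assessed according to evaluation of the relevant symptoms and reported as the percentage of patients in whom there is an improvement in or resolution". This applies at 6 and 12 months to sleep apnoea, hypertension, diabetes and hyperlipidemia. No threshold for improvement or resolution is given, and the percentage is not tied to having the condition at the start.

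The eligibility criteria admit patients with abdominal adiposity "according to the presence of at least two of the following components of MetS". The listed components are pre-diabetes, type 2 diabetes, hypertension, raised triglycerides and low HDL-C. Each is described by a laboratory value, a blood pressure or current treatment. Sleep apnoea is not listed.

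Two general rules bear on the denominator. Under data analysis: "The statistical analyses will be conducted on an intention-to-treat basis". Under populations for evaluation, all evaluations "will be made with data from all randomized patients, regardless of whether they adhered to the treatment protocol or provided complete data sets".

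**The concern.** There are two separate problems.

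**Basis of judgement.** A patient can enter because of a triglyceride value, a blood pressure reading or a current prescription, and may have no symptom that could change. Symptoms also cannot separate a condition that has resolved from one that is controlled by drugs. The entry criteria need that distinction, because they count treatment as evidence of the condition. Followed as written, the outcome can miss true resolution and can credit resolution where the measurement is still abnormal.

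**Denominator.** Under the general rule, a patient without hypertension would count among the patients for hypertension but could never improve. Each percentage would then mix two quantities: how many patients in the arm had the condition, and how many of those improved. A reader would take it as an improvement or resolution rate, which it is not.

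**Working it through.** **1. Basis, side by side.**

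| Condition in the outcome | Definition in the eligibility criteria | Stated basis for change |
|---|---|---|
| Diabetes | HbA1 > 6.5 or glucose > 6.1 | symptoms |
| Hypertension | 130/85 mmHg or on treatment | symptoms |
| Hyperlipidemia | triglycerides > 1.7 mmol/L or on treatment; HDL-C < 1.03 (men) or < 1.29 mmol/L (women) or on treatment | symptoms |
| Obstructive sleep apnoea | none | symptoms |

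The mismatch is documented for three of the four conditions. For sleep apnoea the article gives no definition at all. The amount of misclassification cannot be calculated from the document.

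**2. Who can have each condition.** Raised triglycerides plus low HDL-C satisfy the two-component rule, so a patient can enter with neither diabetes nor hypertension. Entry therefore does not ensure that any one of the four conditions is present in every patient.

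**3. Size of the dilution.** The article states no comorbidity rate, effect or power, so there is no figure to reproduce. The rates below are assumptions for illustration: 80% versus 30% improved among affected patients, 20 per arm (from the randomization section) and two-sided alpha 0.05.

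- Percentage over all randomised = prevalence × percentage among affected. At 50% prevalence: 0.5 × 0.80 = 0.40 and 0.5 × 0.30 = 0.15.
- Difference = prevalence × (0.80 − 0.30). At 50% prevalence: 0.5 × 0.50 = 0.25.
- Relative risk = 0.80/0.30 = 2.67, unchanged if prevalence is equal in the arms.
- Power ≈ Φ{[Δ − 1.96 √(2p̄(1−p̄)/n)] / √([p₁(1−p₁) + p₂(1−p₂)]/n)}, with n = 20 over all randomised, or n = 20 × prevalence among affected.

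| Baseline prevalence | Shown over all randomised | Difference (points) | Power, all randomised | Power, affected only |
|---|---|---|---|---|
| 30% | 24% vs 9% | 15 | 0.24 | 0.40 |
| 50% | 40% vs 15% | 25 | 0.42 | 0.63 |
| 70% | 56% vs 21% | 35 | 0.63 | 0.79 |
| 90% | 72% vs 27% | 45 | 0.84 | 0.89 |

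The difference among affected patients is 50 points in every row. The power figures are normal approximations with the number affected held at its expected value, and they are rough where that number is small (6 per arm at 30%).

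**4. Chance imbalance in prevalence.** The standard deviation of the difference in prevalence between two arms is √(2 × prevalence × (1 − prevalence)/20). At 50% this is √0.025 = 0.158, or about 16 points. In simulation, a gap of 20 points or more occurred in about 22% to 27% of trials at prevalences of 30% to 70%. As an example of such a gap, take 8/20 versus 12/20 affected with 60% improving in both arms. The expected display is 0.6 × 8/20 = 24% versus 0.6 × 12/20 = 36%, a relative risk of 0.67 with no true difference.

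**5. Type I error.** Fisher's exact test was simulated with 50% prevalence and 60% improvement in both arms (6,000 trials). It rejected in 0.029 of trials over all randomised and in 0.027 among affected patients only. Both are below 0.05.

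**The case against.** **The denominator is inferred.** The outcome section does not name all randomised patients, and speaking of improvement in a condition may presuppose having it. The population rule is mainly about adherence and incomplete data. This stands as far as it goes: nothing says outright that unaffected patients are scored as failures. But that rule covers every evaluation, and nothing in the outcome section limits it. The default therefore points to all randomised patients.

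**Symptoms may be meant loosely.** The background section calls metabolic syndrome a combination of symptoms, and the abbreviation list includes laboratory indices that the visible text does not use, such as HOMA-IR. Follow-up laboratory work may appear in the figures or the additional file, and cut-offs may sit in a fuller protocol or analysis plan. This is plausible, and absent cut-offs are not held against the article. The point is narrower: the basis that the outcome section does state differs from the entry definitions, and loose usage in the background does not reconcile them.

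**Entry might make the conditions universal.** The criteria add that patients are inadequately controlled despite treatment for their diabetes, hypertension and lipid disorders. That describes the disorders a patient has; the two-component rule still does not require all of them.

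**Stronger readings to resist.** A reader might infer that the assessors know the arm. The outcome section names no assessor, and the blinding section states independent evaluation with a blinded outcome analyser. A reader might also infer that odds ratios from logistic regression will be presented as relative risks. The data analysis section says that "categorical variables will be reported as the relative risk" where appropriate, in the sentence on simple comparisons. It names logistic regression separately, for multivariable analysis, so no error is shown.

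**Conclusion.** The point holds in two limited parts. First, the stated basis for judging diabetes, hyperlipidemia and hypertension is inconsistent with the protocol's own definitions and can misclassify resolution, to an extent that cannot be quantified here. Second, the denominator is not limited to affected patients, and the general rule makes all randomised patients the default. The percentages would then depend on baseline prevalence and be mislabelled as improvement or resolution rates.

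On the assumed rates, prevalences of 30% to 90% shrink a 50-point difference to between 15 and 45 points. The loss of power is largest at low and middle prevalence. All of this rests on assumed prevalence and improvement rates and on the all-randomised reading.

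A reader might conclude that the percentages invalidate the comparison. That goes too far: the test keeps its type I error, the expected relative risk is unchanged when prevalence is balanced, and a prevalence gap between arms is chance, not bias. This is a secondary outcome, and the remedy is mainly one of wording.

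**What to change.** In the comorbidity outcome, replace the symptom basis as follows.

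- **Resolution:** judge diabetes, hypertension and lipid disorder by the measurements and treatment status used for entry (HbA1c or glucose, blood pressure, triglycerides, HDL-C), repeated at V3 and V4. State which lipid components make up hyperlipidemia.
- **Improvement:** define it on the same measures. The entry thresholds establish presence only, so they do not supply this definition.
- **Denominator:** report each percentage among patients with that condition at V1, by allocated arm. Eligibility is settled before randomisation, so entry-defined status gives a subgroup that preserves the randomised comparison.
- **Sleep apnoea:** state a criterion and report only patients with the condition documented by it at baseline.
- **Population rule:** add a sentence saying that condition-specific percentages use this restricted denominator.

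The cost is fewer patients per condition, so intervals based on fewer observations, and the measurements must be available at 6 and 12 months. The article already schedules data collection at those visits, but its visible text does not confirm that these measurements are taken then.
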